### **Toxicology**

In GLP studies, pyronaridine was shown to produce hepatic, splenic and renal inflammatory changes in the rat with a NOEL of 12 mg/kg. In the dog the NOAEL was 15 mg/kg there was some incidence of reduction in erythrocyte indices and at high doses precipitation of yellow material in many tissues, presumed to be the drug substance or metabolites.

Artesunate induced a reduction in food consumption and body weight loss in rats and dogs. The NOEL in the rat was 30 mg/kg and the NOAEL 6 mg/kg in the dog. There was also a reduction in erythrocyte indices.

When administered together there was no evidence of the toxicity of either drug being enhanced.

### **Genotoxicity**

Artesunate may be considered to be free from mutagenic or clastogenic potential.

Pyronaridine has shown positive genotoxic results in one study *in vitro*, however the *in vivo* studies showed no genotoxic effects up to doses which resulted in exposures of about 25 times the expected human  $C_{max}$  after the third dose. Studies of the genotoxicity of the combination of the two drugs provided no evidence of any effects other than those for pyronaridine alone.

### ***Phase I Data with Pyronaridine-Artesunate Combination***

A randomised, blinded phase I clinical study has been conducted with the fixed ratio combination of pyronaridine artesunate (3:1). The protocol combined multiple objectives of single and multiple dose-rising phases as well as food-effect and drug-interaction sub-studies. Four dose levels of pyronaridine artesunate were investigated in the single and multiple rising dose parts (6:2; 9:3; 12:4; 15:5 mg/kg pyronaridine artesunate, respectively). The study recruited healthy male and female subjects aged 19-40 years: 9 per group (7 active 2 placebo) in the single-rising dose; 10 per group (5 male, 5 female) in both the interaction and food effect studies; 8 per group (6 active 2 placebo) in the multiple dose-rising part. Dose escalation was approved by medical reviewers and Investigators on review of safety data. Assessments consisted of safety evaluation (vital signs, ECG, lab tests, adverse events), up to 14 days after dosing. With single and multiple dosing (once daily for 3 days), no individual clinically significant sustained drug-related changes were recorded in vital signs, ECGs and clinical laboratory tests. The adverse events at doses studied were minor or moderate in nature and resolved without sequelae. No serious or severe adverse events were reported. The adverse event profile was consistent those reported in the literature for both components and are predominantly gastrointestinal in nature. No subject discontinued treatment due to adverse events including vomiting. In summary, the combination was well-tolerated up to and including the dose ratio of 15:5 mg/kg,

with only mild or moderate adverse events, including gastrointestinal effects, observed. No significant food effect was reported and there was no notable drug interaction effect.

Moreover the pharmacokinetic profile of the combination therapy revealed that the artesunate component has a short elimination half-life and the pyronaridine component has an intermediate half-life. Blood pyronaridine and plasma artesunate exhibited approximate linear dose proportionality over the dose range: 6:2 to 15:5 mg/kg (pyronaridine:artesunate respectively) in the single dose study. Absorption was rapid, with a  $T_{max}$  of 1.6 to 4.8 h. for pyronaridine and 0.6 to 0.9 h. for artesunate. The elimination half-life ranged from 6.6 to 9.7 days for pyronaridine, 0.44 to 0.53 h. for artesunate, and 0.9 to 1.5 h. for DHA. Pharmacokinetic analyses show that blood pyronaridine concentrations accumulate with repeated daily doses, whereas plasma artesunate and DHA concentrations do not. Furthermore the food effect study does not suggest any clinically relevant effect of food on the bioavailability of either compound.

The data from the phase I study supported the transition for the combination product into adult patients with acute uncomplicated malaria. The pharmacokinetic profile after single and multiple doses regimens supports once-daily dosing.

### ***Phase II Clinical Study in acute uncomplicated *P. falciparum* malaria***

A phase II dose ranging study (SP-002-05) has been conducted in acute uncomplicated *P. falciparum* malaria patients between the ages of 15 and 60 years with doses of pyronaridine:artesunate of 6:2, 9:3 or 12:4 mg/kg. Patients were followed to 42 days post therapy, with a primary endpoint of 28 day PCR-corrected adequate clinical and parasitological response (ACPR). Four hundred and seventy seven patients were recruited in 8 sites in 6 countries in Africa and South-East Asia.

Parasitaemia cleared within approximately 30 hours at all dose levels. The cure rate at Day 28 was greater than 95% in all three dose levels.

Adverse events were as anticipated with the class of drugs, including those related to clinically significant laboratory parameters. Central reading of all ECGs,

demonstrated no notable effects, either during the dosing period or out to Day 28. Of the 6 serious adverse events (SAEs) reported in 4 patients, only 2 were regarded as possibly or probably related to pyronaridine artesunate administration.

A further dose escalation study (SP-003-05) is being conducted, in paediatric patients between 2 and 14 years old (body weight between 10 and 40 kg inclusive) with uncomplicated *P. falciparum* malaria at a study site in Gabon. Doses of pyronaridine artesunate of 6:2, 9:3 or 12:4 mg/kg are being studied in cohorts of 15 patients per dose level. Pharmacokinetics are studied in each patient. Additional endpoints include PCR-corrected and crude ACPR at Day 28 and safety outcomes including laboratory parameters, adverse events and ECGs.

## 2. STUDY OBJECTIVES

The primary objective of this clinical study is to compare the efficacy and safety of the fixed combination of pyronaridine artesunate (180:60 mg) with that of standard chloroquine therapy in children and adults with acute, uncomplicated *Plasmodium vivax* (*P. vivax*) malaria.

### 3. METHODS AND INVESTIGATIONAL PLAN

#### 3.1. Study Design Overview

The study is designed as a multicentre, randomized, double-blind, double-dummy, parallel group, comparative trial.

Patients will be randomized to receive either oral pyronaridine artesunate (180:60 mg tablets), plus chloroquine-placebo or oral chloroquine (155 mg tablets), plus pyronaridine artesunate-placebo, once a day for 3 consecutive days. Patients will be followed for 42 days after the first study drug administration, the primary efficacy endpoint occurring at Day 14.

For patients who complete the study up to Day 28 and who have normal G-6-PD-activity, a 14-day course of primaquine (15 mg/day) shall be administered starting on Day 28, after all required assessments have been performed, to complete their radical cure. Patients who are deficient in G-6-PD and who complete the study up to Day 28 will be treated as per country policy. For all patients, a final safety assessment will be performed on Day 42.

#### 3.2. Selection of Study Population

This study will be conducted in a total of 456 male and female children ( $\geq 20$  kg body weight) and adult patients suffering from acute symptomatic uncomplicated *P. vivax* malaria recruited from trial sites located in South East Asia and India. The study will be randomised, with a maximum of 100 patients to be included per site.

Patients will be randomised in a 1:1 ratio to one of the following two treatment arms:

- Active-pyronaridine artesunate plus chloroquine-placebo
- Active-chloroquine plus pyronaridine artesunate-placebo

##### 3.2.1. Inclusion criteria

Patients must fulfil the following inclusion criteria to be eligible for enrolment in the study:

1. Male or female patients between the age of 3 and 60 years, inclusive.
2. Body weight between 20 kg and 90 kg with no clinical evidence of severe malnutrition.
3. Presence of acute uncomplicated *P. vivax* mono-infection confirmed by:

- a. Fever, as defined by axillary/tympanic temperature  $\geq 37.5^{\circ}\text{C}$  or oral/rectal temperature  $\geq 38^{\circ}\text{C}$ , or history of fever in the previous 24 hours (history of fever must be documented) **and**,
  - b. Positive microscopy of *P. vivax* with parasite density  $\geq 250/\mu\text{L}$  of blood (including at least 50% of asexual parasites)
4. Written informed consent, in accordance with local practice, provided by patient and/or parent/guardian/spouse. If the patient is unable to write, witnessed consent is permitted according to local ethical considerations.
5. Ability to swallow oral medication.
6. Ability and willingness to participate based on information given to patient or parent or guardian and access to health facility.

### 3.2.2. Exclusion criteria

To be eligible for enrolment in the study, patients must NOT meet any of the following criteria:

1. Presence of a mixed *Plasmodium* infection.
2. Presence of other clinical condition requiring hospitalization.
3. Presence of significant anaemia, as defined by  $\text{Hb} < 8 \text{ g/dL}$ .
4. Known history or evidence of clinically significant disorders such as cardiovascular (including arrhythmia, QTc interval greater than or equal to 450 msec), respiratory (including active tuberculosis), hepatic, renal, gastrointestinal, immunological (including active HIV-AIDS), neurological (including auditory), endocrine, infectious, malignancy, psychiatric or other abnormality (including recent head trauma).
5. Known history of hypersensitivity, allergic or adverse reactions to pyronaridine, chloroquine or artesunate or other artemisinins.
6. Known history of hypersensitivity, allergic or adverse reactions to chloroquine, primaquine and related agents.
7. Known active Hepatitis A IgM (HAV-IgM), Hepatitis B surface antigen (HBsAg) or Hepatitis C antibody (HCV Ab).
8. Known seropositive HIV antibody.
9. Have received any antimalarial treatment in the preceding 2 weeks, as determined by history and, whenever feasible, by screening test.
10. Have received antibacterial with known antimalarial activity in the preceding 2 weeks.

11. Have received any investigational drug within the past 4 weeks.
12. Liver function tests (AST/ALT levels) more than 2.5 times the upper limit of normal range.
13. Known significant renal impairment as indicated by serum creatinine levels of more than 1.4 mg/dL.
14. Female patients of child-bearing potential must be neither pregnant (as demonstrated by a negative pregnancy test) nor lactating, and must be willing to take measures to not become pregnant during the study period.
15. Previous participation in the present clinical trial with pyronaridine artesunate.

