### Entry Laboratory Screen

At a minimum the results of the following tests must be available before the patient is randomised:

- ◆ Haemoglobin
- ◆ Urea
- ◆ Sodium
- ◆ Potassium
- ◆ Blood glucose
- ◆ Alanine aminotransferase (ALT/SGPT)
- ◆ Aspartate aminotransferase (AST/SGOT)
- ◆ Creatinine
- ◆ Pregnancy test (Urine hCG)

If the results of baseline laboratory evaluations of other haematology, biochemistry and urine parameters fall outside of the normal range and are regarded as clinically significant, the Study Medical Monitor should be notified.

The estimated total volume of blood that will be drawn from each patient in this study is presented in Table 2.

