**\* at selected sites only**

Laboratory values that fall outside a clinically accepted reference range must be evaluated and commented on by the Investigator, and graded according to the DMID Toxicity Scale for Determining Severity of Adverse Events (Attachment 7). Generally, clinically significant abnormalities that represent a change from baseline and could be considered to be detrimental are to be recorded as adverse events. It is anticipated that a fall in haematological parameters such as haemoglobin may occur during treatment and, in general falls of up to 2 g/dL need not be reported as adverse events unless that fall is considered to be detrimental to the patient. Detrimental changes in differential white cell count (other than clinically significant falls in neutrophils) should only be reported as adverse events

if their change is considered to be contributing to deterioration on the patients' condition.

Investigators must document their review of each laboratory report by signing and dating each report. Laboratory data will be transcribed into the CRF. The laboratory reports are to be kept with the CRF until source data verification has been performed by the monitor and then it should be filed with the source document for the study.

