| Vomiting           | 1 episode/day                                           | 2-3 episodes per day                        | 4-6 episodes per day                                                     | Greater than 6 episodes per day or Intractable Vomiting                  |

| ELECTROLYTES          |                            |                            |                             |                                                         |
|------------------------------|----------------------------|----------------------------|-----------------------------|---------------------------------------------------------|
|                              | GRADE 1             | GRADE 2             | GRADE 3              | GRADE 4                                          |
| CREATININE            |                            |                            |                             |                                                         |
| 2 Years- 12 Years of age     | 0.7-1.0 mg/dL              | 1.1-1.6 mg/dL              | 1.7-2.0 mg/dL               | >2.0 mg/dL                                              |
| Greater than 12 Years of age | 1.0-1.7 mg/dL              | 1.8-2.4 mg/dL              | 2.5-3.5 mg/dL               | >3.5 mg/dL                                              |
| Hypernatraemia               |                            | <145-149 mEq/L             | 150-155 mEq/L               | >155 mEq/L or abnormal sodium AND mental status changes |
| Hyponatraemia                |                            | 130-135 mEq/L              | 129-124 mEq/L               | <124 mEq/L or abnormal sodium AND mental status changes |
| Hyperkalaemia                | 5.0-5.9 mEq/L              | 6.0-6.4 mEq/L              | 6.5-7.0 mEq/L               | >7.0 mEq/L or abnormal potassium AND cardiac arrhythmia |
| Hypokalaemia                 | 3.0-3.5 mEq/L              | 2.5-2.9 mEq/L              | 2.0-2.4 mEq/L               | <2.0 mEq/L or abnormal potassium AND cardiac arrhythmia |
| Hypercalcaemia               | 10.5-11.2mg/dL             | 11.3-11.9 mg/dL            | 12.0-12.9 mg/dL             | >13.0 mg/dL                                             |
| Hypocalcaemia                | 7.8-8.4 mg/dL              | 7.0-7.7 mg/dL              | 6.0-6.9 mg/dL               | <6.0 mg/dL                                              |

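### The single creatinine limit in exclusion 13 is not age-adjusted and admits children aged 3 to 12 with values that are already Grade 2 on the protocol's own paediatric scale

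*Protocol*

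**What the plan says.** Section 3.2.1 admits "Male or female patients between the age of 3 and 60 years, inclusive", with a weight of 20 to 90 kg. Section 3.2.2 gives two renal exclusions. Exclusion 13 is numeric: "Known significant renal impairment as indicated by serum creatinine levels of more than 1.4 mg/dL". The synopsis repeats it, and neither place varies it by age. Exclusion 4 is a matter of judgement: it begins "Known history or evidence of clinically significant disorders such as cardiovascular" and goes on to list renal disorders among others.

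The preceding laboratory criterion, exclusion 12, is relative rather than absolute: "Liver function tests (AST/ALT levels) more than 2.5 times the upper limit of normal range".

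Section 5.2.2 requires out-of-range laboratory values to be "graded according to the DMID Toxicity Scale for Determining Severity of Adverse Events (Attachment 7"). The paediatric part of Attachment 7 has two creatinine rows, one labelled "2 Years- 12 Years of age" and one for children over 12. Adult creatinine is graded in multiples of the upper limit of normal (ULN).

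Under the entry laboratory screen in section 5.2.2, creatinine is on the list introduced by "At a minimum the results of the following tests must be available before the patient is randomised".

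**The concern.** One absolute value serves as the indicator of significant renal impairment from age 3 upwards, while the scale attached to the same protocol treats a given creatinine value as more abnormal at 12 or under than above 12. A site that finds 1.3 mg/dL in a young child would grade it 2 under Attachment 7, yet the protocol's only numeric renal criterion would let the child in.

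The Toxicology summary in section 1 reports renal inflammatory changes in rats given pyronaridine, and section 1 describes the paediatric dose-escalation study as still under way. An entry limit that is looser, by the protocol's own grading, in the youngest patients is therefore worth correcting. It also has a modest effect on safety reporting. A child who enters above the local normal range cannot show a normal-to-abnormal shift, and a rise from 1.4 to 1.6 mg/dL would not change the grade.

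**Working it through.** No sample-size or error-rate formula is involved. The check sets the exclusion limit against the grading bands, assuming creatinine reported to one decimal.

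**Inputs.** Exclusion 13: above 1.4 mg/dL is excluded, so 1.4 and below passes. Attachment 7, paediatric creatinine (mg/dL):

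- 2 to 12 years: Grade 1 = 0.7-1.0; Grade 2 = 1.1-1.6; Grade 3 = 1.7-2.0; Grade 4 above 2.0.
- Over 12 years: Grade 1 = 1.0-1.7; Grade 2 = 1.8-2.4; Grade 3 = 2.5-3.5; Grade 4 above 3.5.

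**Creatinine, value by value.**

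| Creatinine (mg/dL) | Exclusion 13 | Grade, 12 or under | Grade, over 12 |
|---|---|---|---|
| 0.7-0.9 | admitted | 1 | none |
| 1.0 | admitted | 1 | 1 |
| 1.1, 1.2, 1.3, 1.4 | admitted | 2 | 1 |
| 1.5, 1.6 | excluded | 2 | 1 |
| 1.7 | excluded | 3 | 1 |
| 1.8-2.0 | excluded | 3 | 2 |
| above 2.0 | excluded | 4 | 2 or higher |

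The Grade 2 band for the younger group holds 6 one-decimal values (1.1 to 1.6). Of these, 4 are admitted and 2 excluded. The limit is 1.4 / 0.7 = 2.0 times the lower bound of Grade 1 in that group. The worst admitted grade is 2 at 12 or under and 1 above 12.

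**The same comparison for the other two laboratory limits.**

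- Haemoglobin: below 8 g/dL is excluded. The worst admitted value, 8.0, is Grade 2 for adults (8.0-9.4) and Grade 2 for children over 2 years (7.0-9.9).
- AST/ALT: above 2.5 x ULN is excluded. The worst admitted value, 2.5 x ULN, is Grade 1 for adults (1.25-2.5) and Grade 1 for children (1.1-4.9).

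The paediatric haemoglobin and AST/ALT rows have no split at age 12, so the worst admitted grade is also the same on either side of that age. Of the three limits, only creatinine becomes looser by grade at the younger age.

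**The case against.** The strongest reply is that Attachment 7 grades the severity of adverse events and laboratory changes; it is not an eligibility standard. Nothing in the protocol says that a Grade 2 value bars entry, and the haemoglobin limit admits Grade 2 as well. This stands: a reader might infer a formal contradiction between section 3.2.2 and Attachment 7, and there is none. The point rests instead on the age difference in the worst admitted grade, which the haemoglobin limit does not share.

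A second reply is that the AST/ALT limit is not aligned to grade boundaries either, since 2.5 x ULN is the top of Grade 1 in adults but lies inside Grade 1 in children. That is correct, but the misalignment runs towards greater strictness in children, the opposite of creatinine.

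A reader might also infer that the renal exclusion does not work in young children. The documents do not support that. It removes 1.5-1.6 mg/dL and everything in Grades 3 and 4, and exclusion 4 bars clinically significant renal disorders at any age, although without a number. Nor can it be shown that adults are protected more strictly: adult creatinine is graded against a ULN that the protocol does not give in mg/dL.

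Finally, the harm to the analysis is limited. Section 9.5.2 builds laboratory shifts from normal ranges and from baseline, not from grades. Section 5.2.2 has the investigator evaluate each out-of-range value, and biochemistry is repeated on Days 3, 7 and 28. Randomisation is 1:1 in blocks by site, so raised baseline values would not systematically favour one arm.

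**Conclusion.** The point holds in a limited form. Exclusion 13 is not age-adjusted. By the protocol's own paediatric scale it admits children of 12 or under with 1.1-1.4 mg/dL at Grade 2 and adolescents over 12 at no more than Grade 1. It is less strict in young children, not ineffective.

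This assumes that adolescents are graded on the over-12 paediatric row and that values are reported to one decimal. How many children are affected cannot be computed: the protocol gives neither the expected number aged 12 or under nor their creatinine distribution, and the 20 kg minimum weight limits entry of the youngest. The primary endpoint, sample size and efficacy analysis are untouched. It is a low-cost correction to a paediatric safety criterion that should be made.

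**What to change.** Reconcile exclusion 13, in both the synopsis and section 3.2.2, with the age bands of Attachment 7 by making the creatinine criterion age-referenced. One way is to state it against the local age-specific upper limit of normal, which works only if the local laboratory ranges are themselves age-specific. The cut-off is a clinical choice for the sponsor, and none is proposed here.

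The cost is one line in two places. No test is added, because creatinine must already be known before randomisation. The downside is that some young children with raised creatinine may be screened out; how many is unknown.

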### **3.3. Patient Discontinuation or Protocol Violation**

A patient may withdraw consent at any time, without prejudice for further follow up or treatment by the study site.

A patient may be discontinued prematurely from the study if the Investigator decides that a patient should be withdrawn for safety reasons, due to an adverse event of such a nature or intensity (including abnormal laboratory finding), where study drug withdrawal or withdrawal from the study is advisable. Information concerning any adverse event and symptomatic treatment given must be recorded on the case record form (CRF). If the adverse event is serious, the Investigator must notify the Sponsor or its designee immediately and the reporting procedures described in the safety section must be followed. Definitions and reporting requirements for adverse events are provided in section 5.2.4.

Self or third party administration of antimalarial (or antibiotics with antimalarial activity) treatment other than for treatment failure will be classified as a protocol violation. A list of Forbidden Medication is provided in Attachment 5.

In the case of a patient vomiting the first dose (Day 0) within 0 to 30 minutes of study drug administration, a repeat full dose will be given. If patient vomits the study drug on either the second (Day1) or third day (Day 2) of dosing or if the patient vomits a re-administered dose on Day 0, they will not be re-dosed but will be withdrawn from the study. A patient who is withdrawn due to vomiting should receive rescue medication, after having completed end of study (Day 28) assessments.

A patient who terminates participation after any study drug administration for any reason will be considered as having discontinued from the study and will have

end of study (Day 28) procedures performed. The reason for discontinuation will be recorded on the CRF. If a patient is discontinued for an adverse event, the Investigator will continue to follow the patient until resolution or until no further medically relevant information can be expected.

Every effort must be made to schedule a follow-up visit for patients who fail to return to the study site after administration of the study drug. Women who inadvertently become pregnant during the study must be followed to full term and the outcome of the birth fully documented on a specific form provided by Sponsor.

